## Abstract

**Introduction:**

The ProSPoNS trial is a multicentre, double-blind, placebo-controlled trial to evaluate the role of probiotics in prevention of neonatal sepsis. The present protocol describes the data and methodology for the cost utility of the probiotic intervention alongside the controlled trial.

**Methods and analysis:**

A societal perspective will be adopted in the economic evaluation. Direct medical and non-medical costs associated with neonatal sepsis and its treatment would be ascertained in both the intervention and the control arm. Intervention costs will be facilitated through primary data collection and programme budgetary records. Treatment cost for neonatal sepsis and associated conditions will be accessed from Indian national costing database estimating healthcare system costs. A cost–utility design will be employed with outcome as incremental cost per disability-adjusted life year averted. Considering a time-horizon of 6 months, trial estimates will be extrapolated to model the cost and consequences among high-risk neonatal population in India. A discount rate of 3% will be used. Impact of uncertainties present in analysis will be addressed through both deterministic and probabilistic sensitivity analysis.

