#### Decision model

In view of the shortcomings of treatment effect measure coming from a single RCT, we also propose using a model-based approach which will allow synthesising information from all sources for a health technology enabling us to explore scenarios not explicitly found in the trial data. Moreover, the modelling approach would enable to estimate the long-term benefits of intervention incorporating quality of life measures. Furthermore, it allows accounting for uncertainties present in assumptions and data used for economic evaluation, which has implications for policy question under consideration. The clinical outcomes from trial would be sepsis episodes averted as an effect of probiotics use in the intervention arm. Quality of life (QUALY) is a preferred utility measure for economic analysis; however, there is no EQ-5D version for neonates. Therefore, in order to assess the long-term effects, we propose to use ‘DALY’ as the measure of health outcome, which accounts for both disability and quality of life. A decision-analytic model following a systematic approach in bringing together evidence on clinical effectiveness, health-related disability of life and costs associated with the probiotic intervention as compared with placebo will be used with the aim to provide information on whether the reduction in neonatal sepsis incidence justifies the incremental costs. Figure 2 depicts the decision model for the proposed study.

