#### Outcome measures

Primary outcome measure for economic evaluation (within-trial CUA) would be sepsis episodes and related deaths averted in the intervention arm as compared with the placebo arm, which translates to gain in life years and DALYs averted as long-term measure.

Data requirements: data requirements for economic evaluation are tabulated in table 1.

**Table 1 T1:** Data requirements for economic evaluation

Data type	Significance for the model	Source of data
Demographic	Estimate the baseline parameters Estimate target population	Primary data collection; Census of India
Treatment effects and incidence of adverse events	Efficacy and safety parameters Cost estimation Outcome assessment	RCT Database
Background mortality data	Estimate natural mortality in the target population	SRS, Published literature
Utilities	Estimate DALY as long-term outcome measure	Global Burden of Diseases estimates (2011)
Resource use and price data	Cost estimation	Primary data collection; NHSC—Prinja *et al*
Epidemiological data	Estimate baseline risk of clinical events	Published literature; Primary data collection (Control arm of the RCT)

NHSCD, National Health Systems Costing Database; RCT, randomised control trial; SRS, Sample Registration System.

Utility data would allow incorporating the relative impact of a health technology (ie, probiotics) on the neonatal health outcomes in terms of disability burden. This will be estimated as DALYs averted. Utility data would be obtained from Global disease burden estimates 2017. Cost data are important drivers of cost-effectiveness, as they quantify the resource consumption associated with the use of health technologies.

Decision-analytic model would be populated with cost data from the societal perspective: direct medical and non-medical cost borne by patients; and direct medical cost borne by the healthcare system. A National Health Systems Costing Database (NHSCD) to estimate healthcare system’s costs in India has been developed.^12^ Data on patient’s out-of-pocket (OOP) expenses would be collected during the conduct of the RCT as primary data.

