### Effectiveness assessment

Prevention of severe sepsis in the early neonates will prevent the long-term morbidity like neurodevelopmental disability risk associated with sepsis^13^ and reduce mortality due to pneumonia, meningitis and neonatal sepsis and hospital admissions due to any infectious diseases.^14^

We propose to use the short time horizon to assess the sepsis averted as a result of probiotics supplementation for 1 month and model the change in DALYs in the intervention group as a long-term measure.

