Objective	To assess the incremental cost per DALY averted with use of probiotics for prevention of neonatal sepsis compared the placebo	Besides effectiveness, evidence on cost-effectiveness is mandatory for adoption of treatment/intervention under public policy
Target Audience/policy use	National Health Mission (NHM) Any other	This intervention is to be implemented under RMNCH programme
Method	Both model and trial based	Short –term outcome estimates will be used for trial Use of model-based CEA will enable us to assess long-term outcomes (and sub-group analysis)
Perspective	Societal perspective	OOP burden associated with sepsis management among LBW neonates
Analytic horizon	6 months	To model long-term outcomes (DALYs)
Costs	Health system costs (Vivomixx cost; Cost of routine HBPNC care; cost of illness management etc.) OOP expenditures (doctor’s consultation; bed charges; drug costs; vitamin/mineral supplement costs; investigations; procedures; informal payments; travel cost etc.	Both health system and patients’ costs as per societal perspective considered for CEA
Outcomes	Sepsis episodes and deaths averted DALYs Hospitalisation averted Life years gained	In line with study design (cost-effectiveness/cost-utility analysis)
Discount rate	3%	As per Indian reference case

CEA, Cost Effectiveness Analysis; DALYs, disability-adjusted life years; HBPNC, home-based postnatal care; LBW, low-birth weight; OOP, out-of-pocket.

Total cost will be comprised of cost of intervention, cost of management of sepsis and associated complications and patient costs as OOP. Similarly, total cost in the control arm will be estimated in the absence of intervention. Annual discount rate of 3% will be used wherever applicable. In the present study, both model-based approach as well as trial data would be used. Data management and analysis will be done using MS-Excel.

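### The abstract and Table 2 give the model a 6-month horizon for costs and consequences, which conflicts with its aim of counting long-term DALYs; years of life lost and sequelae need their own stated horizon.

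*Protocol article*

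**What the plan says.** All references are to the protocol article.

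- **Abstract, Methods and analysis.** The outcome is incremental cost per DALY averted, and the next step is put this way: "Considering a time-horizon of 6 months, trial estimates will be extrapolated to model the cost and consequences". The horizon is therefore attached to the model and to health consequences as well as costs.
- **Costing, Table 2, row on analytic horizon.** The entry is 6 months, justified by "To model long-term outcomes (DALYs". The outcomes row of the same table lists life years gained.
- **Decision model.** On the purpose of modelling: "the modelling approach would enable to estimate the long-term benefits of intervention incorporating quality of life measures".
- **Outcome measures.** Episodes and deaths averted are to be converted into life years and DALYs as a long-term measure.
- **Effectiveness assessment.** Preventing severe sepsis "will prevent the long-term morbidity like neurodevelopmental disability risk associated with sepsis". A short horizon is proposed for sepsis averted, and the plan is then to "model the change in DALYs in the intervention group as a long-term measure".
- **Costing, text after Table 2.** "Annual discount rate of 3% will be used wherever applicable".

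No life expectancy, life table or lifetime horizon is stated anywhere.

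**The concern.** Nearly all of the DALY gain from preventing a neonatal death lies in years of life after infancy, and neurodevelopmental disability also accrues over years. Six months cannot hold either. Trial follow-up runs to day 60 of life (Study details), so a 6-month model adds only about four months to what the trial observes.

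Cost per DALY averted is the stated objective and is meant to inform adoption in a public programme. If the horizon in the abstract and Table 2 is applied to DALYs, the denominator of that ratio loses almost all of its mortality part. If the long-term wording elsewhere is applied, it does not. Two analysts working from this text could report results that differ by tens of fold.

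**Working it through.** The article gives no expected DALYs per death and no expected cost per DALY, so there is no figure of the plan's own to reproduce. The check compares the credit for one averted death under the two readings.

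**Inputs from the article**
- Horizon: 6 months = 0.5 year (abstract, Table 2).
- Discount rate: r = 3% per year (Table 2 and the text after it).
- Age at enrolment 3 to 7 days (Background); follow-up to day 60 of life (Study details). Deaths are therefore placed near birth, at 1 month and at 2 months, leaving 0.5, 5/12 and 4/12 year inside a horizon counted from birth.

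**Assumed, because the article does not give it**
- Remaining life expectancy L = 60, 70 or 80 years.

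**Formula.** Discounted life-years over a span T: (1 − e^(−0.03T)) / 0.03.

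**Credit if years of life lost stop at 6 months**
- Death near birth: (1 − e^(−0.015)) / 0.03 = 0.496
- Death at 1 month: (1 − e^(−0.0125)) / 0.03 = 0.414
- Death at 2 months: (1 − e^(−0.010)) / 0.03 = 0.332

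**Credit over a lifetime, and its ratio to the truncated credit**

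| L (years) | Discounted life-years | Ratio, death near birth | Ratio, death at 1 month | Ratio, death at 2 months |
|---|---|---|---|---|
| 60 | 27.82 | 56.1 | 67.2 | 83.9 |
| 70 | 29.25 | 58.9 | 70.6 | 88.2 |
| 80 | 30.31 | 61.1 | 73.2 | 91.4 |

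Using r = ln(1.03) instead changes the ratios by about 1% (for example 56.1 becomes 56.6). Undiscounted, a death near birth gives 60/0.5 = 120 to 80/0.5 = 160.

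**Adding acute disability.** Assume a disability weight of 0.2 for 14 days, which is 0.2 × 14/365 = 0.0077 DALY per episode. With case fatality c, the ratio per episode is (c × lifetime credit + 0.0077) / (c × truncated credit + 0.0077).
- c = 30%, L = 60, death near birth: (0.3 × 27.82 + 0.0077) / (0.3 × 0.496 + 0.0077) = 53.4
- c = 5%, same case: 43.1
- c = 2%, same case: 32.1

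These three ratios leave out long-term sequelae, which a 6-month cut would also remove.

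**Effect of the discount rate.** 1.03^(−0.5) = 0.985, so over 6 months the 3% rate changes a value by at most about 1.5%. It has real work to do only if outcomes run well past 6 months.

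**The case against.** The strongest reply is that the article never says years of life lost stop at 6 months. Years of life lost are ordinarily the remaining life expectancy at the age of death, whenever the window for modelled events closes. A 6-month decision tree can count deaths and attach the full life expectancy at the end of each branch. Several places fit that reading: the Effectiveness assessment separates a short horizon for sepsis from DALYs as a long-term measure, Table 2 lists life years gained, Table 1 calls for background mortality data, and a 3% rate is set. The decision-tree figure is not available here, so the branch values cannot be checked.

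This stands as far as it goes. A reader might infer that the plan does truncate DALYs and that its cost per DALY will be inflated 55- to 75-fold. The documents do not support that as a fact about the plan; it follows from one literal reading. The reply does not remove the conflict, because the abstract ties 6 months to consequences and Table 2 ties it to DALYs by name. Nor does any passage supply the lifetime horizon that the kinder reading needs.

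Three further limits are accepted:
- The Discussion says that a longer horizon than that of RCTs is often needed. This conflicts only weakly, since 6 months already exceeds the 60-day follow-up.
- The fold figure for cost per DALY needs years of life lost to dominate and incremental cost to be positive and equal under both horizons. The plan itself anticipates cost offsets. With net cost near zero or negative, the fold figure has no decision meaning.
- The difference in Global Burden of Disease editions is real but separate, and adds nothing to the size of this point.

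**Conclusion.** The 6-month horizon, as stated and justified in the abstract and Table 2, conflicts with the plan's own long-term aims. It bears on the main result and should be corrected. This is not a detail left to a fuller document, because the article states the parameter twice.

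The size is conditional. If years of life lost are cut at 6 months, each averted death earns at most about 0.5 life-year instead of roughly 28 to 30 (L = 60 to 80 years, 3%). The mortality part of DALYs averted is then understated about 55- to 75-fold for deaths by about 1 month, and about 84- to 91-fold at 2 months. Counting acute disability lowers the ratio but leaves it in the tens under the values tried. Carrying the figure over to cost per DALY also requires the cost and dominance conditions given above. If full life expectancy is attached to each death, the understatement of years of life lost does not arise and the defect is one of wording.

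**What to change.** In the abstract and Table 2, replace the single horizon with two:

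- a short horizon for sepsis events and within-trial costs;
- a lifetime horizon for years of life lost (life expectancy at age of death, from a named life table) and for long-term sequelae, discounted at 3%.

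Report an undiscounted analysis and the 6-month result as scenarios. Say whether later care costs of sequelae are counted over the same period as their disability, so that numerator and denominator match.

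The cost is a wording change and a standard life-table calculation, with no new data collection. The downside is small: assumptions about long-term survival and sequelae become explicit, and the planned probabilistic sensitivity analysis can vary them.

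Separately, name one Global Burden of Disease edition. Under Outcome measures, Table 1 cites "Global Burden of Diseases estimates (2011" while the text below it says "Utility data would be obtained from Global disease burden estimates 2017".

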**Ethics and dissemination:**

Has been obtained from EC of the six participating sites (MGIMS Wardha, KEM Pune, JIPMER Puducherry, AIPH, Bhubaneswar, LHMC New Delhi, SMC Meerut) as well as from the ERC of LSTM, UK. A peer-reviewed article will be published after completion of the study. Findings will be disseminated to the community of the study sites, with academic bodies and policymakers.

**Registration:**

The protocol has been approved by the regulatory authority (Central Drugs Standards Control Organisation; CDSCO) in India (CT-NOC No. CT/NOC/17/2019 dated 1 March 2019). The ProSPoNS trial is registered at the Clinical Trial Registry of India (CTRI). Registered on 16 May 2019.

**Trial registration number:**

CTRI/2019/05/019197; Clinical Trial Registry.

Strengths and limitations of this studyThis would be the first study evaluating cost-effectiveness of using probiotic intervention among low-birth weight newborn infants in India.This study would inform incremental costs per disability-adjusted life year averted with use of probiotics, which will be key for prioritising resource allocation in view of other competing demands for child health, therefore crucial for public policy decisions.Data from the RCT would be complimented with the use of a model-based approach to explore scenarios beyond the trial data.Generalisability and external validity of findings from economic evaluation concurrently performed with the main study may not represent the same treatment effects and costs as in routine clinical practice.

## Introduction

There is progress towards attaining the third Sustainable Development Goal (SDG) of under-five (U5) mortality of 25 per 1000 live births by 2030, in India. Neonatal mortality rate is the most important contributing factor of the U5 mortality.^1 2^ Further decline in neonatal mortality may require newer interventions for prevention or treatment of neonatal infections like meningitis, pneumonia, septicaemia that result in more than a quarter of the 1 million neonatal deaths every year in India.^2^

The ProSPoNS trial^3^ proposes to evaluate the role of probiotics in prevention of neonatal infections (sepsis) among the vulnerable group of low-birth weight infants contributing the highest rates of morbidity and mortality. A larger sample size and precise outcome measures differentiate this trial from the earlier conducted pilot study that showcased a 21% non-significant decline in morbidity due to neonatal sepsis in the intervention arm. Considering the 30% prevalence of low-birth weight (LBW) in India and 30% mortality due to neonatal sepsis, even a small decline in the incidence of sepsis would translate to a large number of new born lives saved.^3^

If the intervention is proven to be efficacious, it would be important to know whether it is also a cost-effective intervention. There are few examples in the literature where economic evaluations have been conducted on other effective interventions to prevent neonatal sepsis.^4 5^ It cannot be overemphasised that along with clinical effectiveness of interventions, an estimate of economic effectiveness either in terms of costs or utilities (disability-adjusted life years; DALYs and Quality adjusted life years; QALYs) is required to make correct choices about their inclusion in public health programmes. This is of immense importance in presence of multiple competitive options where prioritisation is needed.

Ranjeva *et al*^6^ have quantified the scope of the public health and economic burden of neonatal sepsis in Sub-Saharan Africa. However, evidence on the health economics aspect of neonatal sepsis prevention effect of probiotics has not been ascertained so far. We propose to evaluate the cost utility of probiotic intervention for prevention of neonatal sepsis within the ProSPoNS trial.

## Background

ProSPoNS trial is a phase III multicentre randomised, double-blind placebo-controlled trial, being conducted at six study sites across India. It is a global Health trial funded by the UK Research and Innovation.

The Study is ongoing at six sites across India: Jawaharlal Institute of Postgraduate Medical Education and Research (JIPMER), Puducherry, Mahatma Gandhi Institute of Medical Sciences (MGIMS), Wardha, King Edward Memorial Hospital (KEM Hospital), Pune, Asian Institute of Public Health (AIPH), Bhubaneswar (with recruitments from SCB Medical College and Hospital, Cuttack), Subharti Medical College (SMC) and Lala Lajpat Rai Memorial Medical (LLRM) College District women hospital, Meerut and Lady Hardinge Medical College (LHMC), Kalawati Saran Children’s Hospital (KSCH), Delhi. The primary objective is to estimate a 30% reduction in the incidence of neonatal sepsis in the intervention arm with daily supplementation of 1 mL (10 billion CFU/mL) of Vivomixx drops over a period of 30 days in 0–2-month-old LBW infants. 6144 low-birth weight (between 1500 g and 2500 g) infants would be recruited to the study from the six study sites located in Bhubaneswar, Meerut, New Delhi, Puducherry, Pune and Sewagram, between ages 3 and 7 days of life.

### Theory of change

More than one-third of the estimated four million neonatal deaths around the world each year are caused by severe infections, and a quarter—around one million deaths—is due to neonatal sepsis/pneumonia alone. Panigrahi *et al* in their study which was conducted in the year 2017 reported that the Culture-confirmed incidence of sepsis as 6.7/1000 births with 51% Gram negatives (Klebsiella predominating) and 26% Gram positives (mostly Staphylococcus aureus). The SDG for child survival cannot be achieved without substantial reductions in infection-specific neonatal mortality.^1^ Due to non-specific signs and symptoms, sepsis is difficult to diagnose. The chances of recovery and survival depend on the correct diagnosis, referral, reaching a facility and adequate treatment by appropriately trained health workers and high-quality services.

Low-birth weight is one of the important indirect causes of deaths in neonates accounting for 40%–80% of neonatal deaths worldwide.^2^ LBW neonates are immune compromised and manifest poor cognitive functions.^7^ Since LBW infants are more prone to infections, neonatal mortality and morbidity may be decreased by preventing neonatal infection.

Antibiotic therapy is the mainstay of current therapeutic management of neonatal infections. For serious infections in new borns and young infants, there is a lack of guidelines on rational antibiotic use.^8^ In the absence of rapid diagnostics, non-judicious use of antibiotics contributes to the rising antimicrobial resistance. Antibiotic overuse is linked with disturbing the gut ecosystem. The problem of drug resistance outweighs the fast pace of newer generation antibiotic production.

Currently, there are no preventive interventions available for neonatal sepsis other than general measures of hand washing, exclusive breastfeeding, etc. However evaluating immunotherapy with immune globulin, probiotics, myeloid colony-stimulating factors, glutamine supplementation, recombinant human protein C and lactoferrin are being evaluated as adjuvants for the prevention of neonatal sepsis.^9^ Probiotics are non-pathogenic microbes which are capable of exerting positive health effects in the host body through various mechanisms.^10 11^ It acts by suppressing the growth of potential pathogens and their epithelial attachment. It also works by secreting antimicrobial substances or by stimulating host expression of protective molecules. Besides, it can produce a barrier against the harmful pathogens at higher levels. It stimulates the process of immunosuppressive agent’s production in the host which suppress the inflammatory responses or accelerate the immunologic mechanism that clears the infection. Probiotics stimulate normal microbe–microbe and host–microbe interactions positively, thereby enhance the protection provided by commensal flora through competitive interactions, pathogenic antagonism and antimicrobial factors. We hypothesise that immunomodulation/immunopotentiation with probiotics may prove to be an alternative for the prevention of neonatal sepsis. Figure 1 depicts the conceptual framework to prevent sepsis episodes among 0–2 months neonatal population with use of probiotics.

**Figure 1 F1:**
[figure not shown]
Conceptual framework to prevent neonatal sepsis using probiotics.

